### Nurse training

3.2

The ICU nurses will receive training on CGM, including how to insert and configure the sensor before starting the trial. The training and improvement of the adherence to the protocol will be provided by the principal investigator, an expert in Diabetes Education and has been trained by the manufacturer of the CGM Dexcom G7 (Dexcom, San Diego, CA).

### Intervention

3.3

This study consists of a comparison of two randomized groups:
Experimental group: Critically ill patients admitted to the ICU with hyperglycaemia using CGM, as the basis for glycaemia management decisions.Control group: Critically ill patients admitted to the ICU at TH with hyperglycaemia using POC‐G, as the basis for glycaemia management decisions.

Both groups will have a Dexcom G7 CGM sensor. Each sensor requires a 30‐min warm‐up period. The Dexcom G7 CGM averages glucose values every 5 min, obtaining a total of 288 glucose readings over 24 h, ranging from 40 to 400 mg/dL (2.2–22.2 mmol/L). The sensor will be placed on the upper arm or abdomen. If a computerized tomography (CT) scan is needed, the CGM can be used without issue. However, in the case of magnetic resonance imaging (MRI), the sensor must be removed. The duration of each sensor's use will be a maximum of 10 days, but will end upon the patient's discharge, the need for MRI or in the case of death.

#### Blinding

3.3.1

The patients involved in the study will be blinded, meaning they will not know whether they are in the experimental group using real‐time CGM or in the control group. The blinding process will be straightforward: both groups will have the same receiver and sensor inserted. In the experimental group, nurses will be able to see glucose values displayed on the receiver, while in the control group, the receiver will not show any values, effectively functioning as a ‘placebo’ sensor. This set‐up ensures that the patients cannot distinguish between the groups. Only the nurses will be aware of the group assignments, while the integrity of patient blinding is maintained.

#### Control group

3.3.2

The CGM in the control group will be blinded, connected to the Dexcom G7 receiver to save the data, which will be downloaded later to the Clarity platform (Dexcom) for retrospective analysis.

POC‐G will be performed according to the usual protocol of TH. In case of glycaemic decompensation, POC‐G will be performed every 6 h and/or as needed. For patients with continuous intravenous insulin infusion, POC‐G may be performed every 2 h, 1 h or even every 15 min, depending on the stability of glucose levels and the nurse's judgement.

Therefore, there will be no intervention that modifies the usual treatment of patients in the ICU. The glucometer used in the centre is CareSens® Dual (Pascual y Furio Diabetes, Paterna, Valencia).

#### Experimental group

3.3.3

The Dexcom G7 will be connected to the Dexcom G7 receiver, serving as an external monitor for nurses to use the data in real time. The data will be downloaded to Clarity. The following alarms will be set:
Glucose level at 220 mg/dL (12.2 mmol/L).Glucose level at 80 mg/dL (4.4 mmol/L).Trend arrows.Upcoming urgent hypoglycaemia: An alert that notifies whether glucose is predicted to be <55 mg/dL (<3 mmol/L) in 20 min.Glucose level at <55 mg/dL (<3 mmol/L).

Additionally, the clinical team can perform as many POC‐G tests as they deem necessary. If the CGM values do not match the POC‐G values, the CGM can be calibrated. It should be noted that the comparison of POC‐G and CGM cannot be considered if the POC‐G was obtained during a rapid glucose change. Calibration can only be done when the patient's glucose is stable, when there is no active insulin (more than 3 h have passed since the last administration) and when there are no trend arrows.

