**Results:**

The primary variable considered will be time in range (TIR), with secondary outcomes including, time above range (TAR), time below range (TBR), number of POC‐G measurements, incidence of hyperglycaemia and hypoglycaemia, and mortality. Hypothesis testing will use the Kolmogorov–Smirnov test to assess data normality, with appropriate statistical tests applied, considering a *p*‐value <.05.

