## BACKGROUND

1

The care of critically ill individuals has undergone a substantial transformation; intensive care units (ICUs) have evolved into highly specialized facilities.^1^

Critically ill patients exhibit blood glucose levels >180 mg/dL (10 mmol/L)^2^ with a prevalence of 77.8%–86.2%,^3^, ^4^ all contributing to heightened morbidity, mortality and safety concerns.^5^, ^6^, ^7^

The gold standard for ICU care is capillary blood glucose measurement, but there are instances where arterial blood or central venous blood samples are employed. These diverse approaches fall under the category of point‐of‐care glucose (POC‐G). Critically ill patients require three to six POC‐G measurements per day. In cases of intravenous insulin infusion, the frequency of POC‐G measurements may increase.^2^

Glucose control technology has advanced to continuous glucose monitoring (CGM), offering frequent measurements and their trends. Although CGM holds theoretical promise in improving hypoglycaemia detection and management compared with traditional POC‐G, it is important to note that it has not received approval from the U.S. Food and Drug Administration for inpatient use. However, during the COVID‐19 pandemic, the first studies appeared indicating that CGM can significantly enhance glycaemic management.^2^ CGM systems offer the opportunity to remotely monitor patients, providing alerts and the chance to prevent hypoglycaemia.^8^, ^9^

During the COVID‐19 pandemic, Agarwal et al. emphasized the feasibility, acceptability and reliability of CGM as a complementary measurement to POC‐G testing. A notable decrease in the frequency of POC‐G measurements, up to 71%, was observed when CGM was employed.^10^, ^11^, ^12^, ^13^, ^14^, ^15^

For CGM to be commercialized for people with diabetes in outpatient settings, a mean absolute relative difference (MARD) of less than 10% is required.^16^ However, in the ICU, an MARD below 15% is considered accurate, although a consensus is needed. Additionally, the Clarke Error Grid requires 98% of values to fall within zones A and B.^17^

Analysed articles found that CGM is accurate in ICUs with an MARD of 9.3%–13.9%, even during extracorporeal membrane oxygenation.^12^, ^13^, ^14^, ^18^, ^19^, ^20^, ^21^ The Clarke Error Grid results showed that 98.0%–99.7% of CGM readings fell within safe zones.^13^, ^14^, ^19^

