### Setting and sample

3.1

HCB has 62 ICU beds and 47 intermediate care beds, totalling 109, distributed across 6 specialized ICUs, with an annual population of 13 262. The sample size was calculated using the approximation of two independent proportions via the GRANMO Sample Size Calculator (https://apisal.es/GRANMO). Accepting an alpha risk (*α*) of .05 and a beta risk (*β*) of .2 in a two‐tailed test, a sample size of 376 individuals is deemed necessary. The expected proportion for the control group in terms of TIR is 35%, while for the experimental group, it is assumed to be 50%. An estimated loss of 10% has been considered. The ARCSINUS approximation was used.

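### The sensor that evidently scores time in range may be calibrated to POC-G in the experimental arm, while no calibration is described for the blinded control arm, so the primary outcome may be measured differently by arm

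*Protocol article*

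**What the plan says.** All references are to the protocol article.

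- **Outcome.** The abstract states: "The primary variable considered will be time in range (TIR").
- **Device.** Section 3.3: "Both groups will have a Dexcom G7 CGM sensor". Sections 3.3.2 and 3.3.3 send both arms' data to the Clarity platform.
- **Control arm.** Section 3.3.2: "The CGM in the control group will be blinded, connected to the Dexcom G7 receiver to save the data", for later retrospective analysis. Section 3.3.1: "in the control group, the receiver will not show any values". Section 3.3.2 mentions no calibration.
- **Experimental arm.** Section 3.3.3 allows calibration when sensor and POC-G disagree: "values, the CGM can be calibrated". It then limits this: "Calibration can only be done when the patient's glucose is stable", with more than 3 h since the last insulin and no trend arrows.
- **Who knows the allocation.** Section 3.3.1 blinds patients but not nurses.
- **Sensor accuracy.** The Background reports that "CGM is accurate in ICUs with an MARD of 9.3%–13.9"%. It gives no signed (mean) error.
- **Planned effect.** Section 3.1 assumes 35% for control and 50% for the experimental group, a difference of 15 points.

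**The concern.** The control arm's hidden sensor has no stated use except to store data for analysis, so TIR must come from the sensor trace in both arms. That trace can be adjusted toward POC-G in one arm, at the discretion of staff who know the allocation. In the other arm nobody can see a reason to adjust it.

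Randomization balances patients. It does not balance a measurement procedure that differs by arm. If the sensors read high or low on average in these patients, the error would be reduced in the experimental arm to the extent that calibration happens, and would stay in full in the control arm. An arm difference in measured TIR could then arise with identical true glucose. With glucose centred near the upper limit of the range, sensors that read high in the control arm would create a false benefit. Sensors that read low would hide a real one. TAR, TBR and mean glucose, where taken from the same trace, would be affected too.

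**Working it through.** **1. The plan's own figure.** The sample size is not in dispute; it is reproduced only to fix the scale. With the arcsine approximation, h = 2·asin(√0.50) − 2·asin(√0.35) = 0.3047, and n per arm = 2·((1.960 + 0.842)/0.3047)² = 169.09. With 10% loss, 2 × 169.09/0.90 = 375.75, which rounds to the stated 376. The effect to compare with is 50 − 35 = 15 points.

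**2. Inputs for the illustration.**

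- Range 80-180 mg/dL: inferred from the hypo- and hyperglycaemia limits in section 3.3.4. The article does not state the TIR limits.
- Glucose normal with mean 180 and SD 45 mg/dL, the same in both arms: assumed.
- Mean proportional sensor bias b of ±5% or ±10%: assumed. MARD cannot supply it, because MARD is absolute error and can coexist with zero mean bias.
- Fraction f of experimental sensor time that is fully corrected by calibration: unknown, shown at 1 and 0.25.

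**3. Formula.** Measured TIR(b) = Φ((180/(1+b) − 180)/45) − Φ((80/(1+b) − 180)/45).

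- b = 0: Φ(0) − Φ(−2.222) = 0.5000 − 0.0131 = 48.7%.
- b = −5%: Φ(0.2105) − Φ(−2.1287) = 0.5834 − 0.0166 = 56.7%.
- b = +5%: Φ(−0.1905) − Φ(−2.3069) = 0.4245 − 0.0105 = 41.4%.

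The control arm shows TIR(b). The experimental arm shows f·TIR(0) + (1 − f)·TIR(b). The spurious difference, experimental minus control, is therefore f·(TIR(0) − TIR(b)).

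| Bias b | TIR(b), % | Difference, f = 1 | Difference, f = 0.25 |
|---|---|---|---|
| −10% | 65.02 | −16.3 | −4.1 |
| −5% | 56.67 | −8.0 | −2.0 |
| 0 | 48.69 | 0 | 0 |
| +5% | 41.39 | +7.3 | +1.8 |
| +10% | 34.95 | +13.7 | +3.4 |

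**4. Sensitivity to the glucose model (f = 1).** With lognormal glucose and CV 30%, a mean of 180 mg/dL gives 55.4% true TIR, and 61.9%, 49.0%, 68.1% and 42.8% at −5%, +5%, −10% and +10% bias. A mean of 200 mg/dL gives 41.5% true TIR, and 48.3%, 35.2%, 55.4% and 29.5%. The shift is about 6 to 7 points per 5% bias and 12 to 14 points per 10%. With normal glucose, mean 200 and SD 60, true TIR is 34.7%, and the readings are 40.4%, 29.7%, 46.8% and 25.5%. The shift is then about 5 to 6 points at 5% and 9 to 12 points at 10%. The order of magnitude does not hang on one choice of distribution.

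**The case against.** **The full-correction figures are a ceiling.** They need every control sensor to carry the same non-zero mean bias and all experimental sensor time to be corrected. Section 3.3.3 makes calibration optional, requires a noticed mismatch, and excludes unstable glucose, recent insulin and trend arrows. Enrolled patients have glucose above 180 mg/dL, and intravenous insulin is expected, so calibration may be infrequent. Time before the first calibration is uncorrected in both arms. This stands, and it is why the results are scaled by f.

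**A reader might infer a bias of 10% or so from the cited MARD.** The documents do not support that: no signed bias is given anywhere.

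**A reader might also infer a second large bias because experimental treatment is guided by the same sensor that scores the outcome.** If sensor errors average to zero across patients (SD 10% assumed), a rough calculation puts this effect at only −1 to +3 points. Such guidance also changes true glucose, so it is not purely a measurement artefact. Section 3.3.4 requires POC-G confirmation for values below 80 mg/dL or outside the sensor range, and a POC-G check for falling values under intravenous insulin. This route is not part of the point.

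**The article is condensed.** Control-arm calibration is absent rather than expressly forbidden, and sensitivity analyses may sit in a fuller document. That is fair as far as it goes. But the article does state a calibration rule, states it for one arm, and hides from the other arm the information needed to trigger it. That is a feature of the design as written, not an omitted detail.

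**Conclusion.** The asymmetry stands on the text, with two inferred links: that TIR comes from the sensor in both arms, and that control sensors are not calibrated. Following the article as written leaves the primary comparison open to differential measurement by arm.

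The direction and size are unknown. Under the stated assumptions, the spurious difference is 7-8 points at 5% bias and 14-16 points at 10% if all experimental sensor time is corrected. It is about 2 and 3.5-4 points if a quarter is, against a planned 15. With zero mean bias, this average-shift calculation gives no difference. The documents support neither a forecast that the result will be distorted by a given amount nor a claim that a positive TIR result would be false. They do support the view that a TIR difference of moderate size could not be separated from a measurement difference without further data. This is worth correcting, but it does not by itself invalidate the design.

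**What to change.** Leave bedside care and the sample size as they are, and add the following to the analysis plan and data collection.

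1. Record every calibration with its time, in either arm.
2. Time-stamp paired sensor and POC-G values. From them, report signed bias and MARD by arm, and before and after calibration.
3. Pre-specify a sensitivity analysis of TIR that applies one POC-G-based correction rule to the traces of both arms, using pairs chosen by the same criteria in each arm. State its limitation: the frequency and triggers of POC-G differ by arm, so the correction is not equally well supported in both.
4. Keep that analysis supportive. Do not make the efficacy claim depend on it, nor on an analysis restricted to pre-calibration data. The latter would cut short experimental traces only, at a post-randomization point selected because the sensor disagreed with POC-G.
5. State in advance that the TIR conclusion will be qualified if sensor bias differs by arm.

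The cost is a little more recording and analysis. POC-G is already measured in both arms, and section 3.4 already plans to cross-reference sensor data with clinical records.

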#### Safety criterion in experimental group

3.3.4

This protocol defines hypoglycaemia as a glucose level <80 mg/dL (<4.4 mmol/L), while it is usually defined as <70 mg/dL (<3.9 mmol/L) in individuals with diabetes. To prevent hypoglycaemia, we have set the threshold at <80 mg/dL (<4.4 mmol/L). Hyperglycaemia is defined as any glucose level >180 mg/dL (>10 mmol/L). For our clinical trial, patient safety is the top priority, so we have established the following safety criteria:

*Values outside the measurement range*: The measurement range of the CGM is 40–400 mg/dL (2.2–22.2 mmol/L). Glucose levels outside this range must be confirmed with a POC‐G value.
*Episodes of hyperglycaemia between insulin doses*: If glucose levels exceed 300 mg/dL (16.6 mmol/L) between insulin doses, and it has been more than 3 h since the last insulin dose, the nurse may alert the medical team to determine whether to administer additional insulin or wait until the next scheduled dose.
*Episodes of hypoglycaemia*: If a value <80 mg/dL (<4.4 mmol/L) is detected, confirmation will be sought through a POC‐G measurement, and the ICU's standard protocol will be followed. This involves administering 10–15 g of intravenous or oral glucose, according to the patient's needs. A new POC‐G measurement will be taken after 15 min. If the POC‐G values recover and the CGM values are accurate, CGM values can be used.
*Intravenous insulin*: During the administration of intravenous insulin, POC‐G control will be performed when glycaemia is <180 mg/dL (10 mmol/L), with trend arrows (↓↓) to confirm the accuracy of CGM values as a safety criterion. In cases of glycaemic stability, CGM values can be used.

The ICU team's decisions will always be considered, and the decision‐making process of the team will be analysed. In case of adverse effects, we will inform the ethics committee.

### Data collection tools and methods

3.4

With consent, data will be collected from health records during the ICU stay and until 90 days post‐discharge. The CGM data will be stored on the Clarity platform, and the results will be cross‐referenced with the clinical records in the SAP (System Analysis Program Development) (SAP SE, Walldorf, Germany) of the HCB. Patient anonymity will always be maintained. All data will be analysed according to the intention‐to‐treat principle. Promoting participant retention is not necessary, because their participation is only during hospital admission.

The data will be coded, with each patient being assigned a number from 001 to 376. Each number will be associated with the patient's medical record number, creating a separate database for the information to be analysed. Only the principal investigator, who is responsible, will have access to this information, maintaining the relationship between each code and the patient's medical record number.

The secure storage and transfer of these data will be done through OneDrive (Microsoft Corp., Redmond, WA), included in the software of the HCB. The data collected will be kept for at least 5 years after completion. Subsequently, personal information will only be retained by the hospital for health care purposes and by the principal investigator for other scientific research purposes. Clarity, OneDrive and SAP will be protected with password.

Given the known safety profile of the device used, the highly controlled environment of the ICU and the ability of the clinical team to respond immediately, it is concluded that a Data Monitoring Committee is not necessary for this trial.

#### Statistical inference

3.5.2

To demonstrate significant differences between the two groups concerning the specific variables posed, a statistical analysis will be performed. First, the normality of the data will be checked using the Kolmogorov–Smirnov test. Based on the results, the most appropriate statistical tests will be used. For all tests, a *p*‐value <.05 (less than the significance criterion, *α* = .05) will be considered, and a confidence level of 95% will be established.

Data will be analysed using JAMOVI (version 2.5.6 or higher). Descriptive statistics will be presented as mean ± standard deviation for continuous variables. Continuous variables expected to follow a normal distribution will be compared between groups using Student's *t*‐test, and analysis of variance (ANOVA) will be used when analysing more than two groups or independent variables. For continuous variables that do not meet the normality assumption, the Mann–Whitney *U* test will be applied, as it is suitable for non‐parametric data.

Categorical and count variables will be analysed with Fisher's exact test for proportion comparisons. For variables with high counts, Poisson regression will be employed to provide a more nuanced analysis.

Morbidity and mortality will be evaluated using Kaplan–Meier survival analysis to estimate event probabilities over time, with differences between groups assessed through log‐rank tests to compare survival curves. Additionally, the analysis will address missing data using multiple imputation techniques to ensure the robustness and reliability of the results.

### Ethical and research approvals

3.6

Ethics approval has been obtained from the Ethical Committee of HCB (Approval number: HCB/2023/0377) and the Bioethics Commission of the University of Barcelona (Institutional Review Board: IRB00003099/CER052429), covering all participating sites.

The devices and platforms used are validated with CE certification for use with people; however, they will be used in a different environment. Therefore, it will be reported to the Spanish Agency of Medicines and Medical Devices (AEMPS) via the NEOPS platform with No. 23‐0039. Informed consent will be obtained by the principal investigator, and the possibility of using the data for ancillary studies will be documented in the consent form.

## DISCUSSION

4

The increasing focus on improving glycaemic management highlights CGM as a significant advancement in this domain. Preliminary data indicate that CGM can enhance glycaemic control, reduce the frequency of invasive blood tests and lower the incidence of glucose‐related complications, thereby improving patient outcomes. The strengths of this study include its prospective, multi‐site design, rigorous methodology and comprehensive data analysis using standardized, validated tools.

This research is expected to pave the way for the adoption of CGM as a standard practice in ICUs, improving the overall quality of care for critically ill patients by reducing the burden on health care providers and enhancing patient safety.

The implementation of CGM in ICU settings has shown substantial promise, particularly during the COVID‐19 pandemic. Agarwal et al. emphasized the feasibility and reliability of CGM as a complementary tool to POC‐G.^10^ Some studies reported significant reductions in invasive procedures like POC‐G.^11^, ^12^, ^13^

The findings of Lu et al. present compelling evidence on the utilization of CGM in critically ill patients. Their study revealed a significantly lower incidence of continuous renal replacement therapy in the CGM group (9.5% vs. 21.4%, *p* = .046).^23^ The experimental trial by Lu et al. serves as a good starting point for researching the use of CGM in the ICU.

Nevertheless, a limitation of the current evidence is that most studies were conducted during the COVID‐19 pandemic, presenting unique challenges and constraints. Future research should aim to validate these findings in non‐pandemic settings to explore the broader applicability and benefits of CGM.

Large‐scale randomized controlled trials are necessary to confirm its efficacy and establish comprehensive guidelines.

## LIMITATIONS

5

The main limitation is the difficulty of obtaining informed consent before the insertion of the CGM because of the critical condition of the patient. To mitigate this limitation, informed consent can be requested from family members. Another potential limitation is the number of participants available or willing to participate. Therefore, motivating the participating nurses will be crucial to obtaining the maximum number of participants.

There is also a possibility of selection bias because of the random assignment of patients to groups, as there may be differences in patient characteristics that could affect the results. Additionally, external factors or uncontrolled variables may influence the study's results.

